## Abstract

**Background:**

College students generally have good knowledge about COVID-19 and may facilitate COVID-19 vaccination in family. The purpose of this study is to understand college students’ willingness to persuade their grandparents to initiate COVID-19 vaccination and the effect of their persuasion.

**Methods:**

A combined cross-sectional and experimental study will be conducted online. In the cross-sectional study (Phase I), eligible participants are college students who are aged ≥ 16 years and have at least one living grandparent aged ≥ 60 years who has/have not completed the COVID-19 vaccination. Participants self-complete Questionnaire A to collect information on the socio-demographics of themselves and their grandparents, their knowledge about older adults’ COVID-19 vaccination, as well as Health Belief Model (HBM) and Theory of Planned Behavior (TPB) predictor variables. The primary outcome at Phase I is college students’ willingness to persuade grandparents to receive COVID-19 vaccines. Those who are willing to persuade grandparents and participate in a follow-up survey will be invited to participate in a randomized controlled trial (Phase II). At Phase II, eligible participants are those who have at least one living grandparent aged ≥ 60 years who completed the COVID-19 initial vaccination series but has/have not received a booster dose. At the baseline, participants self-complete Questionnaire B to collect information on individual grandparents’ COVID-19 vaccination status, attitude towards and intention to COVID-19 booster dose. Participants will then be randomly allocated 1:1 to either intervention arm (one-week smartphone-based health education on older adults’ COVID-19 vaccination plus two weeks’ waiting period) or control arm (three weeks’ waiting period). At the end of week three, participants in both arms self-complete Questionnaire C to collect information on their grandparents’ COVID-19 vaccination status. The primary outcome at Phase II is the uptake rate of COVID-19 booster dose among grandparents. Secondary outcomes include grandparents’ attitude and intention to get a COVID-19 booster dose.

**Discussion:**

No previous study had measured the effect of college students’ persuasion on COVID-19 vaccination uptake in older adults. Findings from this study will provide evidence for innovative and potentially feasible interventions that further promote COVID-19 vaccination in older adults.

**Trial registration:**

Chinese Clinical Trial Registry: ChiCTR2200063240. Registered 2 September 2022.

**Supplementary Information:**

The online version contains supplementary material available at 10.1186/s12889-023-16209-2.

## Background

Coronavirus disease 2019 (COVID-19), caused by the SARS-CoV-2 virus, has caused hundreds of millions of infections and millions of deaths worldwide [1, 2]. Among the whole population, older adults tend to be more prone to serious infections, medical complications and deaths after infection with COVID-19 because of underlying diseases and compromised immunity [3, 4]. In China older adults aged 60 years and older accounted for 31% and 81% of the total infected and death cases of COVID-19 [5]. China is an aging society. The population of people aged 65 years and older was just nearly 165 million in 2019, which brings huge challenges to the prevention and control of COVID-19 in China [6]. Hence, older adults are listed as key groups in China’s ninth edition (the most up-to-date version) of COVID-19 prevention and control plan [7].

COVID-19 vaccination is proven to be effective and safe in preventing deaths and other severe consequences caused by COVID-19 among older adults [8]. Besides, booster vaccination is also essential because of the decline in the titers of antibodies over time after vaccination [9, 10]. With the continuous development of vaccines, countries around the world have successively implemented phased vaccination programs [11, 12]. China implemented a nationwide free vaccination program in January 2021 and started a booster dose in September 2021 [13]. As of July 7, 2022, the number of people aged 60 years and older who have been vaccinated and fully vaccinated, accounted for 89% and 84% of older adults respectively, and more than 170 million older adults have received a booster dose [14]. The rollout of COVID-19 vaccines for older adults in China is generally progressing well, but there are still some problems. First, the coverage of COVID-19 booster vaccination for older adults is suboptimal and reaches a plateau [15]. Second, the vaccination coverage of older adults aged 80 years and older need to be improved [14]. Hence, the promotion of vaccination among older adults needs to be further strengthened.

Various measures have been adopted to promote COVID-19 vaccination uptake. For example, a trial in Sweden found that guaranteed cash incentives increased COVID-19 vaccination uptake by 4% [16]. Some other countries provided non-cash rewards, such as free rice/eggs in mainland China, hummus in Israel, and blenders in India, but the impact of these approaches on vaccination remains largely unassessed [17]. Up to now, there are few cost-effective ways to promote vaccination in older adults. Compared to previous ways of promotion based on money or commodity, a randomized controlled trial in Japan based on evolutionary theory found that an information intervention targeting the fundamental motive of kin care can significantly increase willingness to receive COVID-19 vaccination [18]. Furthermore, most older adults in China preferred to get healthcare information from interpersonal sources, [19] and a survey of vaccination intentions among older adults indicated that recommendations from family members may prompt older adults to agree to vaccinate against COVID-19 [20]. These studies show the importance and potential feasibility of family members in promoting vaccines.

As a family member with good knowledge, attitude and practice (KAP) towards COVID-19, college students may be able to receive and then transfer public health messaging to their older family members [21]. Besides, under the influence of traditional Chinese filial piety culture and modern post-figurative culture, college students usually have a good connection with older adults in their family. Additionally, interventions developed based on intergenerational bond between grandparents and grandchildren have also proven effective in alleviating mental problems of older adults [22]. These all indicate that college students may be a natural group to influence older adults’ health decision making. However, college students’ influence on older adults’ decision making of COVID-19 vaccination, has not been studied.

Our study comprises a combination of a cross-sectional study and a subsequent randomized controlled trial. The cross-sectional study aims to assess college students’ willingness to persuade their grandparents to initiate COVID-19 vaccination and investigate factors associated with their willingness. The randomized controlled trial aims to evaluate the impact of college students’ persuasion on grandparents’ COVID-19 booster dose vaccination.

## Methods and analysis

### Study design and setting

A combined cross-sectional and experimental study will be conducted online in China to understand college students’ willingness to persuade their grandparents to initiate COVID-19 vaccination and the effect of their persuasion.

The study has two study phases (Fig. 1; Table 1), including a cross-sectional study (Phase I) and a randomized controlled trial (Phase II). Electronic informed consent will be obtained at the beginning of both phases.

**Fig. 1 Fig1:**
[figure not shown]
Flow chart of the study

At Phase I, college students will be recruited by convenience sampling. Our online survey will be distributed by college students via the social network including WeChat (WeChat is a social media app developed by Tencent, Shenzhen, China). College students will be asked about their willingness to persuade their grandparents to initiate COVID-19 vaccination. Those willing to persuade and participate in a follow-up survey will be invited to participate in the next phase.

At Phase II, considering the representativeness of the sample, stratified sampling between four regions of China (East, Central, West and Northeast) was conducted when recruiting participants. At this phase, eligible participants will be randomly allocated 1:1 to either intervention arm (one-week smartphone-based health education on COVID-19 vaccination in older adults plus two weeks’ waiting period) or control arm (three weeks’ waiting period). At the end of week three, the actual uptake of grandparents’ COVID-19 vaccination will be obtained via college students.

**Table 1 Tab1:** Schedule of the study events

	Cross-sectional study (Phase I)	Experimental study (Phase II)					
EVENTS	Enrollment	Eligibility reconfirmation	Follow-up				Close-out
TIMEPOINT	Month − 1	0	*Day 1*	*Day 4*	*Day 7*	*Day 8–21*	*Day 22*
ENROLLMENT:							
Eligibility screening	X	X					
Informed consent	X	X					
Allocation		X					
INTERVENTIONS:							
Web-based education package			X	X	X		
Manipulation checks			X	X	X		
Daily short message service (SMS) reminder						X	
ASSESSMENTS:							
Socio-demographics of students and grandparents	X						
Grandparents’ COVID-19 vaccination status	X	X					X
Grandparents’ attitude towards COVID-19 booster dose		X					X
Grandparents’ intention to get COVID-19 booster dose		X					X

### Inclusion criteria

Individuals who meet the following criteria are eligible at Phase I: (1) college students (junior college students, undergraduate students, graduate students) in mainland China, (2) aged 16 years or older, (3) have at least one living grandparent aged ≥ 60 years who has/have not completed the COVID-19 vaccination recommended by Chinese health authority (including not vaccinated, not completed the initial vaccination series or completed the initial vaccination series but has/have not vaccinated a booster dose).

Those who meet the following criteria are eligible at Phase II: (1) have completed Phase I survey, (2) have the willingness to persuade grandparents to receive COVID-19 vaccines, (3) willing to participate in the follow-up study, (4) have at least one living grandparent aged ≥ 60 years who completed the COVID-19 initial vaccination series but has/have not received a booster dose. Considering that the vaccination status of older adults may change during the time interval between the two phases, eligibility of Phase II will be double-checked by the baseline questionnaire at Phase II (Questionnaire B).

### Sample size

At Phase I, we use the formula $$N=\frac{{Z}_{\text{1-}\alpha }^{2}\times p\times (1-p)}{{\delta }^{2}}$$ to calculate the sample size. Given an alpha value of 0.05 and the permissible error δ of 0.02, assuming the proportion of college students willing to recommend vaccination for older adults at home as 50%, a minimum of 2401 subjects are required for this quantitative survey.

At Phase II, we use the formula $$N=\frac{[{Z}_{1-\alpha /2}\times \sqrt{\bar{p}\times \bar{q}\times (1+\frac{1}{k})}+{Z}_{1-\beta }\times \sqrt{{p}_{1}\times {q}_{1}+\frac{{p}_{2}\times {q}_{2}}{k}}{]}^{2}}{({p}_{1}-{p}_{2}{)}^{2}}$$ to calculate the sample size. Using parameter, the rate of booster vaccination in older adults is 2.5%, [23, 24] and this figure is expected to increase to 4 times after information intervention, [25] which requires a sample size of 162 eligible older adults in each group to achieve 80% power at a 2-sided 5% level of significance to detect a net difference. Through the preliminary data in Phase I, at least 101 eligible college students are needed to provide the required sample size of eligible older adults.

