### Cross-sectional study

Data of the cross-sectional study will be collected via Questionnaire A. Participants will receive a symbolic reward (CNY 1, or USD 0.15) after completing the questionnaire. At this phase, the dependent variable is defined as college students’ willingness to persuade grandparents to receive COVID-19 vaccines. The independent variables are grouped into five blocks:

College students’ socio-demographics: sex, age, ethnic, educational background (junior college students, undergraduate students and graduate students), major and monthly household income.College students’ knowledge of COVID-19 vaccination in older adults included 7 items on a 5-point scale (from “1 = strongly disagree” to “5 = strongly agree”). The variable will be transformed to categorical (No, Yes), with a cut-off value determined by restricted cubic spline.HBM predictor variables for college students’ willingness to persuade grandparents to get COVID-19 vaccination: perceived susceptibility (included 2 items), perceived severity (included 3 items), perceived benefits (included 2 items), perceived barriers (included 1 items) and cues to action (included 3 items). Items in the HBM will be measured on a 1–5 scale (from “1 = strongly disagree” to “5 = strongly agree”). The items of perceived severity and cues to action will be reverse-scored.TPB predictor variables for college students’ willingness to persuade grandparents to get COVID-19 vaccination: attitude (included 1 items), subjective norms (included 3 items) and Perceived Behavioral Control (included 1 item). Items in the TPB will be measured on a 1–5 scale (from “1 = strongly disagree” to “5 = strongly agree”).Grandparents’ socio-demographics: sex, age, educational background, type of residence (urban or rural), cohabitation history (living together with grandchildren for one year or more), living conditions (living alone, only with spouse, with other family members, living in pension institutions), outdoor activities (measured by frequency), chronic disease (having one or more of the following: cardiovascular diseases, diabetes mellitus, tumor, chronic respiratory diseases, liver cirrhosis, chronic renal failure, nervous system diseases and mental disease).

In addition, college students’ willingness to participate in Phase II and grandparents’ actual COVID-19 vaccination status after persuasion will also be included in Questionnaire A to select eligible participants for the next phase.

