### Statistical analysis

All analysis will be performed using R (V.3.6.1, Foundation for Statistical Computing, Vienna, Austria). All effects will be estimated with 95% CI and *P* values. Statistical significance will be taken as two-sided *P* values < 0.05.

According to the types of the variables, descriptive statistical analysis will be carried out for all variables and outcomes, including count, frequency, ratio, mean, standard deviation, and so on. To test the reliability of all the Likert’s scale, Cronbach’s α test will be used.

At Phase I, the primary outcome is college students’ willingness to persuade their grandparents to receive COVID-19 vaccine. Considering that older adults will be nested in families, the condition that all participants are independent, as required for general logistic regression, does not hold. Thus, the multilevel logistic regression model will be necessary. Assuming that each college student has a different intercept, we will apply random intercept, fixed slop models to investigate factors associated with college students’ willingness. The fixed effects will be reported as adjusted odds ratio (AOR) while random effects will be reported by variance, intraclass correlation (ICC). The Akaike’s information criterion (AIC) will be used to determine the goodness of fit.

At Phase II, Chi-squared test will be used for between-group comparison of grandparents’ uptake of COVID-19 booster dose. Incidence rate ratio (IRR) and 95% CIs will be calculated with Poisson regression, adjusted for grandparents’ sex, age, type of residence, educational background, cohabitation history, living conditions, outdoors activities and chronic diseases. Subgroup analyses will be conducted according to grandparents’ sex, age, type of residence, educational background, cohabitation history and chronic diseases. We will use ANCOVA to analyze grandparents’ score of attitude towards COVID-19 booster dose and intention to get a COVID-19 booster dose. Outcomes will be assessed using both intention-to-treat (ITT) and per-protocol (PP) sets. The ITT analysis will calculate outcomes for all enrolled grandparents. The PP analysis will only include grandparents of grandchildren who successfully completed the questions embedded within the health education materials and completed a follow-up survey. To account for loss-to-follow-up, we will use multiple imputation by chained equations to impute missing values.

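### The Phase I error of ±2 points for 2401 students holds only for independently sampled students; recruitment runs through students' own networks, and the plan makes no allowance for clustering between students

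*Protocol article*

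**What the plan says.** The Protocol article, Sample size, sets the Phase I inputs: "Given an alpha value of 0.05 and the permissible error δ of 0.02", with the proportion willing taken as 50%. It concludes that "a minimum of 2401 subjects are required for this quantitative survey". The printed formula has Z with subscript 1-α, and it contains no design effect.

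On recruitment, Study design and setting states: "At Phase I, college students will be recruited by convenience sampling". It adds: "Our online survey will be distributed by college students via the social network including WeChat".

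On analysis, Statistical analysis recognises that grandparents are nested in families, says that ordinary logistic regression is therefore unsuitable, and calls for a multilevel model. The model is then specified: "Assuming that each college student has a different intercept, we will apply random intercept, fixed slop models". No level above the student is named.

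The student characteristics listed under Cross-sectional study are "sex, age, ethnic, educational background (junior college students, undergraduate students and graduate students), major and monthly household income". College, region and source of referral are not in that list or in the other four predictor blocks.

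**The concern.** The sample size treats students as independent draws. Students who receive a survey link from one another are likely to share a class, a college or a circle of friends, and people so linked may resemble each other in their willingness to persuade grandparents. Positive correlation between students makes the effective sample size smaller than the number recruited.

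The plan accepts the principle for one source of dependence (several grandparents per student) but does not apply it to the dependence that its own recruitment route may create. A student-level intercept absorbs correlation between grandparents of the same student. It does nothing for correlation between students.

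Two things are at stake in Phase I: the stated precision of the primary outcome, and the standard errors of the adjusted odds ratios for student-level predictors (knowledge, Health Belief Model and Theory of Planned Behavior scores).

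**Working it through.** **Inputs from the Protocol article.** α = 0.05, δ = 0.02, p = 0.50 and N = 2401 (Sample size); two-sided testing (Statistical analysis: "Statistical significance will be taken as two-sided *P* values < 0.05").

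**Inputs assumed.** Cluster size m and intraclass correlation ICC between students. The article gives neither, so a range is shown.

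**Step 1: reproduce the plan's figure.** N = z² p(1-p)/δ².

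- With z = 1.96: 1.96² × 0.25 / 0.02² = 2401. This matches.
- With z = 1.645, as the printed subscript 1-α implies: 1.645² × 0.25 / 0.02² = 1691. This does not match.

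So 2401 was obtained with the two-sided value and with a design effect of 1. The subscript is a misprint, and the number is right for a two-sided 5% level.

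**Step 2: allow for clustering at p = 50%.** DEFF = 1 + (m-1) × ICC. Half-width = 1.96 × √(0.25 × DEFF / 2401), which is 2.0 × √DEFF points. Effective n = 2401 / DEFF.

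| m (assumed) | ICC (assumed) | DEFF | Half-width (points) | Effective n |
|---|---|---|---|---|
| 10 | 0.01 | 1.09 | ±2.09 | 2203 |
| 20 | 0.02 | 1.38 | ±2.35 | 1740 |
| 20 | 0.05 | 1.95 | ±2.79 | 1231 |
| 30 | 0.05 | 2.45 | ±3.13 | 980 |

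At p = 50% there is no slack, so any positive correlation takes the half-width above 2 points.

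**Step 3: let the true proportion differ from 50%.** With independent students the half-width is 1.96 × √(p(1-p)/2401). The design effect at which it reaches 2 points is 0.25 / (p(1-p)).

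| p | Half-width, independent students | ±2 points holds up to DEFF |
|---|---|---|
| 0.5 | ±2.00 | 1.00 |
| 0.7 | ±1.83 | 1.19 |
| 0.8 | ±1.60 | 1.56 |
| 0.9 | ±1.20 | 2.78 |

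At p = 0.9, even DEFF = 2.45 gives 1.20 × √2.45 = ±1.9 points.

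**Step 4: tests on predictors.** If variance is understated by a factor V, a nominal 5% test has true size 2 × (1 - Φ(1.96/√V)).

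- Predictor fully shared within a cluster: V = DEFF. This gives 6% at 1.09, 9.5% at 1.38 and 21% at 2.45.
- Predictor that varies within clusters: V is about 1 + (m-1) × ICCx × ICCy, where ICCx is the predictor's own correlation and ICCy the outcome's. Assuming the two are equal, m = 30 with 0.05 gives 1 + 29 × 0.0025 = 1.07 and a size of about 5.8%. With m = 20 and 0.02 it is 1 + 19 × 0.0004 = 1.01, about 5.1%.

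Individual belief and knowledge scores are more likely to resemble the second case.

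**The case against.** The strongest case on the other side is that no loss of precision has been shown. Cluster size and ICC are assumptions, the article does not describe class or college clusters, and the lowest case above is ±2.1 points. The plan's 50% is the worst case for a proportion. If willingness is high, ±2 points can survive a sizeable design effect (Step 3). The 2401 is also stated as a minimum, and willingness is reported for each grandparent, so there can be more than 2401 responses. All of this stands as a limit on the size of the point. It does not change the fact that ±2 points was derived for independent students, and extra grandparents per student do not remove correlation between students.

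A reader might also infer three stronger things that the article does not support:

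- **That college or network is not recorded, so no later correction is possible.** Cross-sectional study lists the model's variables, not every questionnaire item, and the questionnaires are in additional files that are not shown. Phase II recruitment was stratified by four regions, and the Discussion mentions IP address, so some location information appears to be held.
- **That P values for the knowledge and belief predictors are badly wrong.** The 9.5% and 21% sizes apply to predictors shared within a cluster. For scores that vary mainly between individuals, inflation is probably small.
- **That a corrected margin such as ±2.4 to ±3.1 points should replace ±2.0.** It would rest on guessed correlations and be no better grounded.

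Finally, in a convenience sample no margin of error covers selection bias, and neither a design effect nor cluster-robust errors would repair that. This stands, and it is a reason to call ±2 points nominal.

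**Conclusion.** The point holds in a limited form. The ±2-point error for 2401 students is valid only for independent sampling at p = 50%. The recruitment route makes independence doubtful, and the stated analysis allows for no dependence above the student. Sampling error for the willingness proportion is probably understated, by an unknown amount. Assumed design effects of 1.1 to 2.5 give ±2.1 to ±3.1 points at p = 50%, with smaller half-widths if willingness is far from 50%. Intervals for student-level predictors may be somewhat too narrow, chiefly for those shared within a college or network.

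The conclusion rests on positive correlation between students who recruit one another, which is plausible but not documented. It concerns the Phase I survey only. The subscript is a clerical error that changes no number.

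**What to change.** 1. Record college, or a separate link code for each distributing student, in Questionnaire A. If collection has begun, use college or region data if already held. Region is a coarse substitute: four regions are too few for a random intercept or a robust variance, so it would then enter as a fixed term and absorb only part of the correlation.
2. Add the college or link unit as a random intercept above the student, or use cluster-robust standard errors at that level, for both the willingness proportion and the adjusted odds ratios.
3. In Sample size, describe ±2 points as nominal: it applies to independent sampling and does not cover selection bias from convenience recruitment.
4. Print the Phase I subscript as 1-α/2, in line with the Phase II formula in the same section.

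The cost is one questionnaire item or link code, one model term and two small text edits. Phase I intervals may become slightly wider. No extra recruitment is needed.

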### Randomized controlled trial

Eligibility for Phase II will be judged by Questionnaire A and confirmed by Questionnaire B because COVID-19 vaccination status may change during the interval between the two phases. Eligible participants will be assigned to the intervention or control arm at a 1:1 ratio chronologically, according to the sequentially numbered allocation list, which was determined by a series of random numbers generated with Microsoft Excel 2010 (Microsoft Corp., Redmond, WA, USA) prior to recruitment. College students with the order of enrollment corresponding to the smaller half of random numbers will be allocated to the intervention arm, and the rest will be allocated to the control arm. This experimental study is single-blind whereby participants will be unaware of what interventional message will be given to them. Of note, to ensure the reliability of the data, all the participants will receive a simple investigate training in word and be asked to contact their grandparents before completing the Questionnaire B.

At Phase II, a web-based health education package about COVID-19 will be provided to college students in the intervention arm for one week via the research’s WeChat Official Account (a China-based marketing platform with the functions of gathering followers and sending them targeted content). The intervention arm will receive a 5-min web-oriented multicomponent education package at Day 1, 4 and 7, whereas the control arm will not receive this package, reflecting the situation of older adults receiving COVID-19 booster dose under the influence of the current vaccine promotion policy (Table 3). The intervention package consists of two parts: COVID-19 related information and testimony from older adults who received COVID-19 booster.

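### Phase II: the claim of 80% power at the 5% level holds only for independent grandparents with complete outcomes

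*Protocol article*

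**What the plan says.** The Sample size section prints the standard formula for comparing two independent proportions. Its inputs are a control rate, "the rate of booster vaccination in older adults is 2.5" per cent, and an effect, "this figure is expected to increase to 4 times after information intervention", that is, 10%. On this basis the study "requires a sample size of 162 eligible older adults in each group to achieve 80% power at a 2-sided 5% level of significance". The section adds that at least 101 eligible students are needed to supply these grandparents, without saying whether that is per group or in total.

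The unit of randomisation is the student. Study design and setting says "eligible participants will be randomly allocated 1:1 to either intervention arm", and Randomized controlled trial explains that "College students with the order of enrollment corresponding to the smaller half of random numbers will be allocated to the intervention arm". The unit of analysis is the grandparent: under Statistical analysis, "The ITT analysis will calculate outcomes for all enrolled grandparents".

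That section opens the reasoning for its Phase I model with "Considering that older adults will be nested in families" and concludes that independence does not hold, so a multilevel model is needed. For Phase II it names an ordinary chi-squared test and a Poisson regression, with no term for the student or family. On missing data it says "To account for loss-to-follow-up, we will use multiple imputation by chained equations to impute missing values". Follow-up payments are described under Randomized controlled trial, and the Discussion names loss to follow-up as a risk.

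**The concern.** All eligible grandparents of one student share an arm, a persuader and a household history, so their outcomes are likely to be correlated. A formula for independent people then overstates the information in 162 grandparents. Missing outcomes reduce it further. Multiple imputation deals with missing values in the analysis, but does not in general recover the information that unobserved outcomes would have carried.

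What is at stake depends on the test. If the final analysis allows for clustering, power is below the stated figure. If it does not, the nominal 5% level is exceeded, and the main hazard is a false positive. Either way the article states a property for its primary comparison that the described design does not have.

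**Working it through.** **Inputs from the article.** p1 = 0.025; p2 = 4 × 0.025 = 0.10; two-sided 5%; 80% power; 1:1 allocation; 162 per group; at least 101 students.

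**Inputs assumed.** ICC 0.05 to 0.5; loss 10% to 20%. The article gives neither.

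**Step 1: reproduce 162.** With mean rate 0.0625:

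n = [1.96 × √(2 × 0.0625 × 0.9375) + 0.8416 × √(0.025 × 0.975 + 0.10 × 0.90)]² / 0.075² = 162.3.

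The same formula solved for power at 162 gives 79.9%. The stated figure is therefore reproduced with a design effect of 1 and no loss. On this formula there is no slack: any positive ICC or any loss takes power below 80%.

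**Step 2: grandparents per student (m).**

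- 101 students per group: m = 162/101 = 1.60.
- 101 students in total: m = 324/101 = 3.21.

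**Step 3: clustering, no loss.** Design effect DE = 1 + (m − 1) × ICC; effective size = 162/DE; then the formula of step 1. For example, m = 1.60 and ICC 0.3 give DE = 1.18, effective size about 137 and power 73.0%. These figures apply to a test that accounts for clustering and holds the 5% level.

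| ICC | DE, m = 1.60 | Power | DE, m = 3.21 | Power |
|---|---|---|---|---|
| 0.05 | 1.03 | 78.7% | 1.11 | 75.6% |
| 0.1 | 1.06 | 77.6% | 1.22 | 71.6% |
| 0.3 | 1.18 | 73.0% | 1.66 | 58.1% |
| 0.5 | 1.30 | 68.8% | 2.10 | 48.5% |

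**Step 4: loss, no clustering.** 10% loss leaves 162 × 0.9 = 145.8 per group and 75.6% power. 20% loss leaves 129.6 and 70.6%.

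**Step 5: both, at ICC 0.3.**

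| Loss | m = 1.60 | m = 3.21 |
|---|---|---|
| 10% | 68.4% | 53.7% |
| 20% | 63.3% | 49.0% |

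**Step 6: the test as planned.** A beta-binomial simulation (40,000 runs, 162 grandparents per arm, no loss) applied the chi-squared test without continuity correction and without adjustment for clustering. With m = 1.6 each arm had 101 students; with m = 3.2 it had 51.

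| ICC | m | Type I error (both arms 2.5%) | Rejection at 2.5% vs 10% |
|---|---|---|---|
| 0 | 1.6 | 4.5% | 82.6% |
| 0.3 | 1.6 | 6.9% | 80.5% |
| 0.5 | 1.6 | 8.6% | 79.4% |
| 0 | 3.2 | 4.5% | 82.2% |
| 0.3 | 3.2 | 11.8% | 77.2% |
| 0.5 | 3.2 | 17.8% | 75.3% |

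At ICC 0 the simulated rejection rate is 2 to 3 points above the formula's 79.9%, so the formula results in steps 3 to 5 should be read as approximate to that extent.

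**The case against.** The strongest reply is that nothing has been miscalculated, and that stands. A reader might infer an arithmetic error from 162.3 rounding up to 163; that difference is immaterial.

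A second reply is that the planned test would still reject about four times in five at m = 1.6. That also stands, and it rules out a tempting reading: that the planned analysis would have only 65% to 73% power, so that a null result would be misread as adequately powered. Lower power from clustering presupposes a cluster-adjusted test, which the Phase II analysis text does not name. Under the named test the clustering problem appears mainly as excess false positives. Loss to follow-up, by contrast, reduces power whichever test is used.

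Third, the shortfall may be small. At m = 1.6 and ICC 0.05 to 0.1 it is only 1 to 2 points, which is within the accuracy of the formula. Follow-up is short and paid for. An average of 3.2 eligible grandparents is also high when a person usually has four at most, so the per-group reading of 101 is the more natural one. All of this is fair, but the article gives no figure by which a reader could choose the mild case.

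Fourth, 162 and 101 are minimums without a cap, and the full protocol may provide for over-recruitment. So the article does not show that the trial cannot reach 80%. It shows that the number said to deliver 80% contains no allowance. Finally, imputation that uses baseline attitude and intention could recover a little information, so the point about imputation should not be put absolutely.

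**Conclusion.** The point holds as a fault in a stated property, not in the arithmetic. 80% power at a two-sided 5% level with 162 per group requires independent grandparents and complete outcomes. The article contradicts the first condition in its own Phase I reasoning, which concerns grandparents in the same families, and it plans for failure of the second.

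The direction is clear; the size rests on assumptions. For a test that holds the 5% level, with no loss and ICC 0.05 to 0.5, power runs from about 79% to 69% if the 101 students are per group and from about 76% to 49% if they are the total. Loss of 10% to 20% alone gives about 76% to 71%. With ICC 0.3 and 10% loss the figures are about 68% and 54%. With the unadjusted chi-squared test, no loss and ICC 0.3 to 0.5, rejection stays at roughly 75% to 81%, but type I error is about 7% to 9% (m = 1.6) or 12% to 18% (m = 3.2). The two halves of the claim cannot both be kept.

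**What to change.** Rewrite the Phase II paragraph under Sample size so that it:

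- says whether 101 students is per group or in total, and gives m from the Phase I data;
- gives a range of ICC values that includes low ones, with design effect 1 + (m − 1) × ICC, and an assumed loss rate;
- replaces the 80% with the power, or the detectable difference, that 162 per group then provides;
- says that this figure presupposes a test of the Phase II primary outcome that accounts for clustering by student, and brings the Phase II text under Statistical analysis into line with that.

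The cost is a paragraph and a less favourable stated power. No extra participants are needed for the restatement. If the sponsor prefers to keep 80%, the same formula before any loss asks for 192 per group at ICC 0.3 with m = 1.60, or 270 with m = 3.21.
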